## 8 ASSESSMENT OF SAFETY

### 8.1 Specification of Safety Parameters

Safety outcomes will include:

- Cumulative rate of treatment-emergent adverse events (TEAEs) and adverse drug reactions (ADRs) during the study;
- Cumulative rate of SAEs during the study;
- Discontinuation of treatment (for any reason or due to AEs);
- Clinically significant (assessed by the Investigator) deviations in the results of hematology, blood chemistry and urine laboratory tests compared to baseline (Detailed in Section 4.1.1).

### 8.2 Methods and Timing for Assessing, Recording, and Analyzing Safety Parameters

The corresponding safety endpoints are:

1. Number of TEAEs, recorded during the Study period (Day 1 – Day 270±30) in the NeuroAiD II™ group and in the Placebo group
2. Number of ADRs, recorded during the Study period (Day 1 – 270±30 days) in the NeuroAiD II™ group and in the Placebo group
3. Number of SAEs, recorded during the Study period (Day 1 – 270±30 days) in the NeuroAiD II™ group and in the Placebo group
4. Number of patients who discontinued treatment in the NeuroAiD II™ group and in the Placebo group
  - Due to AE
  - For any reason
5. Number of clinically significant (assessed by the Investigator) deviations in the results of haematology, blood chemistry and urine laboratory tests upon NeuroAiD II™/Placebo treatment completion (Day 180±14) in the NeuroAiD II™ group and in the Placebo group compared to baseline (data of laboratory tests and ECG performed at Screening)

At each study visit, the Investigator will ask patients about their well-being and assess whether any subjective AEs have occurred. The AEs, TEAEs, SAEs and ADRs will be recorded starting from the first IP dose intake (Day 1). Subjects may report to the Investigator the AEs occurring at any other time during the study. All subjects experiencing AEs, whether considered associated with the use of the study drug or not, must be monitored until resolution or stabilization.

Procedures for physical examination, vital signs assessment, 12-lead ECG and laboratory tests were detailed in Section 4. The physical examination results, as well as any changes that have occurred since the last inspection should be described in the primary documents and CRF. Data of physical examination, laboratory tests, vital signs and ECG data will be categorized as “normal”, “abnormal, clinically not significantly” or “clinically significant abnormal”. The clinically significant deviations in results of laboratory or instrumental assessment and physical examination data, vital signs and ECG data should be registered as AEs in eCRF.

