### 3.2.2 Safety

The objective of the study is to assess safety of NeuroAiD II™ (MLC901) compared to placebo, following a course of 6-month treatment in adult patients with long-term cognitive impairment after mTBI.

Safety outcomes will include:

1. Cumulative rate of treatment-emergent adverse events (TEAEs) and adverse drug reactions (ADRs) during the study;
2. Cumulative rate of SAEs during the study;
3. Discontinuation of treatment (for any reason or due to AEs);
4. Clinically significant (assessed by the Investigator) deviations in the results of hematology, blood chemistry and urine laboratory tests compared to baseline (Detailed in Section 4.1.1).

Study safety endpoints are detailed in Table 3.2.

Table 3.2. Study safety outcomes and endpoints

| Outcomes                                                                                                                        | Endpoints                                                                                                                                                                                                                                                                                                                            |
|---------------------------------------------------------------------------------------------------------------------------------|--------------------------------------------------------------------------------------------------------------------------------------------------------------------------------------------------------------------------------------------------------------------------------------------------------------------------------------|
| Cumulative rate of TEAEs and ADRs during the study                                                                              | 
 
Number of TEAEs, recorded during the study period (270±30 days) in the NeuroAiD II™ group and in the Placebo group
 
Number of ADRs, recorded during the study period (270±30 days, from Day 1 up to End-of-Study visit) in the NeuroAiD II™ group and in the Placebo group
 
 |

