## 4 STUDY DESIGN

### 4.1 Description of Study Design

This is a randomized double blind, placebo-controlled, multi-center clinical trial. The overview of the study design is given below in Figure 4.1. This clinical trial will include 182 adults (aged between 18 and 65 years of age) who experienced a mild TBI in the past 1 to 12 months and experience cognitive functioning difficulties as indicated by a score of >30 on the Cognitive Failures Questionnaire (consistent with criteria in the pilot study (21)). Eligible participants will be randomized to receive either NeuroAiD II™ (MLC901) or matching placebo.

The study will consist of 3 periods:

- **Screening** (Day -14..-1)
- **Treatment period** (6 months, Day 1 – Day 180±14), during which patients will daily receive an oral dose of IP or placebo
- **Follow-up period** (3 months, Day 180±14 – Day 270±30), after which final efficacy assessment will be performed

The time period from Screening (Visit 1) to Visit 2 (Day 1, Randomization) will not exceed 14 days. If the patient leaves the study before study completion for any reason, then the Early-Termination visit is performed, which should include all procedures and assessments, planned for the End-of-Study visit on Day 270±30.

[figure not shown]

Figure 4.1. Study design.

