### 8.3 Procedures for Eliciting Reports of and for Recording and Reporting Adverse Event and Concurrent Illnesses

### 8.3.1 Definitions

#### 8.3.1.1 Adverse Event

An Adverse Event (AE) is any untoward medical occurrence in a patient or clinical investigation subject administered a pharmaceutical product and that does not necessarily have a causal relationship with this treatment. An AE can therefore be any unfavorable and unintended sign (including an abnormal laboratory finding), symptom, or disease temporally associated with the use of a medicinal (investigational) product, whether or not related to the medicinal (investigational) product.

Treatment Emergent Adverse Event (TEAE) – undesirable event not present prior to medical treatment, or an already present event that worsens either in intensity or frequency following the treatment.

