### **9.1.3 Safety analysis**

Safety analysis will be performed in the safety population. Regardless of the reason for the completion of the study, the data of all patients who received at least one IP/Placebo dose according to the assignments will be included in the safety analysis.

Adverse events will be coded using MedDRA dictionary. Incidences of TEAEs/SAEs will be calculated for assessment of AEs. Incidences of adverse events reported during the study will be presented as number of patients with AE in total and in each treatment group. Also, number of AEs per each severity category and per causal relationship with the study drug will be presented.

Incidences of adverse events will be compared between the IP and the Placebo group. The proportion of patients **with at least one adverse event** will be compared in the NeuroAiD II™ group and in the placebo group.

Vital Signs, Laboratory tests, Physical examination, ECG, Pregnancy test results will be tabulated by visits. Descriptive statistics by visit and for change from baseline will be summarized. Number of clinically significant (assessed by the Investigator) deviations in the results of haematology, blood chemistry and urine laboratory tests upon NeuroAiD II™/Placebo treatment completion

(Day 180±14) in the NeuroAiD II™ group and in the Placebo group compared to baseline will be tabulated.

No formal statistical testing is assumed for safety analysis.

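### TEAEs and SAEs are counted to Day 270±30 under a TEAE definition with no end, so nominally a third of the adverse-event observation time is off drug and is not shown separately

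*Protocol*

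**What the plan says.** Section 8.2 of the protocol sets three event-count endpoints over the whole study: "Number of TEAEs, recorded during the Study period (Day 1 – Day 270±30", "Number of ADRs, recorded during the Study period (Day 1 – 270±30 days" and "Number of SAEs, recorded during the Study period (Day 1 – 270±30 days" (closing brackets omitted). Table 3.2 in section 3.2.2 and the synopsis use the same window: "Number of TEAEs, recorded during the study period (270±30 days".

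Section 4.1 describes a treatment period of "6 months, Day 1 – Day 180±14), during which patients will daily receive an oral dose of IP or placebo", followed by a follow-up period of "3 months, Day 180±14 – Day 270±30), after which final efficacy assessment will be performed". No study drug is given in follow-up.

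Section 8.3.1.1 defines a TEAE as an "undesirable event not present prior to medical treatment, or an already present event that worsens either in intensity or frequency following the treatment". It sets no limit relative to the last dose. Section 8.2 starts recording at the first dose.

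Section 9.1.3 states: "Incidences of adverse events reported during the study will be presented as number of patients with AE in total and in each treatment group". It also compares the proportion of patients with at least one AE between the arms and plans no formal safety test. It does not divide adverse events by whether onset was during or after dosing.

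**The concern.** The protocol counts adverse events in one window that mixes time on drug with time off drug. With no end to the TEAE definition, a new event about 80 days after the last capsule is as treatment-emergent as one on Day 10. If a drug effect is present only during intake, follow-up adds background events to both arms at the same rate, and any relative contrast moves toward one. In a safety comparison that is the unfavourable direction.

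With no formal test planned, readers will judge adverse events from the descriptive contrasts between arms, so the window behind those contrasts matters. The protocol does tie its laboratory endpoint to treatment completion at Day 180±14, so its event endpoints and its laboratory endpoint rest on different anchors.

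**Working it through.** **Inputs from the protocol.** Treatment runs from Day 1 to Day 180±14, that is, to Day 166–194. The end of study is Day 270±30, that is, Day 240–300 (section 4.1). There are 91 patients per arm (section 9.2).

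**Check of a stated figure.** Section 4.4 gives a maximum participation of 314 days. The visit windows reproduce it: 14 screening days + (270 + 30) = 314. The protocol gives no figure for the off-drug share.

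**Off-drug share** = (end of study − end of treatment) / end of study.
- Nominal: (270 − 180)/270 = 33.3%.
- Lowest: (240 − 194)/240 = 19.2%.
- Highest: (300 − 166)/300 = 44.7%.

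The share is larger for patients who stop early, because section 5.4 keeps them in the study where possible.

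**Model (assumed).** The background rate is constant and equal in both arms. The MLC901 rate ratio is RR on drug and 1 afterwards, with no carry-over.

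**Rate ratio over the whole study** = (RR × 180 + 90)/270.
- RR 2.0: (360 + 90)/270 = 1.67 (1.55 to 1.81 across the visit windows).
- RR 1.5: (270 + 90)/270 = 1.33 (1.28 to 1.40).

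**Proportion with at least one AE** = 1 − exp(−cumulative rate). Write p for the 180-day placebo risk. With RR 2, the on-treatment risks are p on placebo and 1 − (1 − p)² on MLC901. The whole-study risks are 1 − (1 − p)^1.5 and 1 − (1 − p)^2.5. The documents give no AE risk for this population over 6 or 9 months, so p is assumed and shown as a range.

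| Assumed p | Risk difference, on treatment | Risk difference, whole study |
|---|---|---|
| 10% | 9.0 points | 8.5 points |
| 20% | 16.0 points | 14.3 points |
| 40% | 24.0 points | 18.6 points |
| 60% | 24.0 points | 15.2 points |

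At p = 40%, for example, 64.0% against 40.0% on treatment becomes 72.1% against 53.5% over the whole study.

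**Number of events.** Follow-up adds the same expected count to each arm. At p = 40% the background rate is −ln(0.6) = 0.511 events per 180 days, or 46.5 events per 91 patients. On treatment the expected counts are 93.0 against 46.5. Over the whole study they are 116.2 against 69.7. The difference is 46.5 both times. The noise does grow: under a Poisson model with RR 2, the variance of the difference is proportional to 180 × (2 + 1) = 540 on treatment and 360 + 90 + 270 = 720 over the whole study. The signal-to-noise ratio therefore falls by 1 − √(540/720) = 13%.

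**The case against.** The other side has good arguments, and several of them stand.

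- **Event counts.** A reader might infer that any excess on MLC901 is pulled toward no difference. That is not so. The listed endpoints are numbers of events, and their expected difference is unchanged. Dilution affects rate ratios and the proportion with at least one AE. The latter is named in section 9.1.3, and section 3.2.2 describes the outcomes as cumulative rates.
- **On-drug results.** A reader might infer that the protocol shows no safety result while patients take the drug. Section 8.2 compares laboratory deviations at treatment completion and counts treatment discontinuations. Section 9.1.3 tabulates vital signs, laboratory tests, physical examination and ECG by visit. The gap is confined to adverse events.
- **ADRs.** Section 8.3.1.2 requires at least a reasonable possibility of causality, so late background events should add little. The filter is loose, since the ADR categories in 8.3.3 include unlikely related and not applicable, but ADRs are still the least affected.
- **Size.** At a low background risk the loss is slight. In the pilot described in section 2.3.2, three adverse events and one haematuria were seen among 36 MLC901 patients. If each was in a different patient, that is 3/36 to 4/36, or 8% to 11%, near the top row of the table. It is an active-arm figure, and no placebo count is given.
- **The window itself.** The safety objective does not limit itself to time on drug, and follow-up captures delayed, persistent and withdrawal effects. Making an on-treatment window the only main comparison would be a trade-off, not the correction of an error.
- **The SAP.** Section 9.1 defers detail to a SAP that is not shown and may split the tables. Even so, the endpoint window and the open-ended TEAE definition are fixed in the protocol.

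**Conclusion.** The point holds as an inexpensive improvement to a window that the protocol itself fixes. The documents do not support calling the whole-study count wrong. Nominally a third of the adverse-event observation time (19% to 45% across the visit windows) is off drug, and the stated adverse-event summaries do not separate the two periods.

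Under a constant background rate and an effect present only during intake, relative contrasts shrink (2.0 to 1.67, 1.5 to 1.33). The difference in the proportion with at least one AE shrinks by 0.5 points at an assumed 10% 180-day placebo risk and by 5.4 points at 40%. If effects persist or appear after stopping, the dilution is smaller or absent, and the follow-up data are then informative in their own right. Either way, a single pooled count cannot tell the two situations apart.

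**What to change.** In sections 8.2, 8.3.1.1 and 9.1.3, present TEAEs, SAEs and the proportion with at least one AE by arm in two parts: onset on treatment (first dose to last dose plus one lag, fixed before unblinding) and onset in post-treatment follow-up. Align Table 3.2 and the synopsis. Keep the whole-study count beside these, so that delayed or withdrawal effects stay visible.

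No new data are needed. Section 8.3.4 already records AE start and end dates, and sections 4.6 and 6.3 provide intake diaries and capsule counts. The cost is some wording, the choice of one lag and one extra set of tables.

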### 8.3 Procedures for Eliciting Reports of and for Recording and Reporting Adverse Event and Concurrent Illnesses

### 8.3.1 Definitions

#### 8.3.1.1 Adverse Event

An Adverse Event (AE) is any untoward medical occurrence in a patient or clinical investigation subject administered a pharmaceutical product and that does not necessarily have a causal relationship with this treatment. An AE can therefore be any unfavorable and unintended sign (including an abnormal laboratory finding), symptom, or disease temporally associated with the use of a medicinal (investigational) product, whether or not related to the medicinal (investigational) product.

Treatment Emergent Adverse Event (TEAE) – undesirable event not present prior to medical treatment, or an already present event that worsens either in intensity or frequency following the treatment.

#### 8.3.1.2 Adverse Drug Reaction

Adverse Drug Reaction (ADR) – in the preapproval clinical experience with a new medicinal product or its new usages, particularly as the therapeutic dose(s) may not be established, all noxious and unintended responses to a medicinal product related to any dose should be considered adverse drug reactions. The phrase "responses product" means that a causal relationship between a medicinal product and an adverse event is at least a reasonable possibility, i.e., the relationship cannot be ruled out.

Regarding marketed medicinal products: A response to a drug that is noxious and unintended and that occurs at doses normally used in man for prophylaxis, diagnosis, or therapy of diseases or for modification of physiological function.

#### 8.3.1.3 Serious Adverse Event

Serious Adverse Event (SAE) – any untoward medical occurrence that at any dose:

1. Results in death;
2. Is life-threatening;

NOTE: The term "life threatening" refers to an event in which the subject was at risk of death at the time of the event; it does not refer to an event that hypothetically might have caused death if it were more severe.

3. Requires inpatient hospitalization or prolongation of existing hospitalization

NOTE: In general, "hospitalization" means that a given patient has been admitted (usually at least one night) in a medical facility or emergency room for follow-up and / or treatment that could not have been provided during the visit to the doctor or on an outpatient basis. Complications that occur during hospitalization are considered AEs. If a complication lengthens hospitalization or meets other criteria for a SAE, it is considered serious. If there is doubt as to whether the "hospitalization" actually took place, or whether it was necessary, the AE should be considered a SAE. **Scheduled hospitalization to treat a pre-existing condition that did not worsen during this study is not considered a SAE.**

4. Results in persistent or significant disability/incapacity;
5. Is a congenital anomaly/birth defect.
6. Is an important medical event that satisfies any of the following:
  - May require intervention to prevent items 1 through 5 above;
  - May expose the subject to danger, even though the event is not immediately life threatening or fatal or does not result in hospitalization.

SUSAR is any SAE where a causal relationship with the study product is at least reasonably possible but is not listed in the Investigator Brochure (IB), Package Insert, and/or Summary of Product Characteristics.

### 8.3.2 Evaluation of severity

The severity of each AE will be graded (mild, moderate, severe, life-threatening, death) according to the Common Terminology Criteria for Adverse Events (CTCAE) Grading (Severity) Scale version 5

([https://ctep.cancer.gov/protocoldevelopment/electronic\\_applications/docs/CTCAE\\_v5\\_Quick\\_Reference\\_8.5x11.pdf](https://ctep.cancer.gov/protocoldevelopment/electronic_applications/docs/CTCAE_v5_Quick_Reference_8.5x11.pdf))

### 8.3.3 Causality assessment

The relationship of each AE to study medication will be assessed using the following categories:

*Related:* An AE that follows a reasonable temporal sequence from administration of a drug (including the course after withdrawal of the drug), or for which possible involvement of the drug cannot be ruled out, although factors other than the drug, such as underlying diseases, complications, concomitant drugs and concurrent treatments, may also be responsible.

*Not Related:* An AE that does not follow a reasonable temporal sequence from administration of a drug and/or that can reasonably be explained by other factors, such as underlying diseases, complications, concomitant drugs and concurrent treatments.

The relationship of each ADR to study medication will be assessed using the following categories:

*Conditional / Unclassified* Event or laboratory test abnormality with more data for proper assessment needed, or additional data under examination

*Unlikely related* An event or laboratory test abnormality, with a time to drug intake that makes a relationship improbable (but not impossible), underlying diseases, complications, concomitant drugs and concurrent treatment provide plausible explanation

*Possibly related* Event or laboratory test abnormality, with reasonable time relationship to drug intake, which could also be explained by disease or other drugs. Information on drug withdrawal may be lacking or unclear

*Probably related* Event or laboratory test abnormality, with reasonable time relationship to drug intake, which is unlikely to be attributed to disease or other drugs. Response to IP withdrawal is clinically reasonable. Rechallenge is not required.

|                           |                                                                                                                                                                                                                                                                                                                                                                                                                               |
|---------------------------|-------------------------------------------------------------------------------------------------------------------------------------------------------------------------------------------------------------------------------------------------------------------------------------------------------------------------------------------------------------------------------------------------------------------------------|
| Definitely related | Event or laboratory test abnormality, with plausible time relationship to drug intake which cannot be explained by disease or other drugs. The response to withdrawal is plausible (pharmacologically, pathologically).

Event definitive pharmacologically or phenomenologically (ie, an objective and specific medical disorder or a recognized pharmacologic phenomenon).
Rechallenge satisfactory, if necessary. |
| Not Applicable     | Report suggesting an adverse reaction, which cannot be judged because information is insufficient or contradictory, data cannot be supplemented or verified                                                                                                                                                                                                                                                                   |

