### 8.3.4 Documentation and reporting of adverse events

All AEs will be documented in the AE page of the CRF, whether or not the investigator concludes that the event is related to the drug treatment. The following information will be documented for each event:

- Event term (preferably, diagnosis).
- Dates of the beginning and the end of AE.
- Frequency: intermittent, continuous.
- Severity: CTCAE grades
- Causal relationship between the event and administration of study drug or study procedure (not related, conditional, unlikely related, possibly related, probably related, definitely related, not applicable).
- Action concerning study drug (drug withdrawn, dose not changed, dose reduced/increased, unknown, not applicable).
- Outcome of event (recovered, recovering, not recovered, resolved with sequelae, fatal, unknown).
- Seriousness (serious, non-serious).

Information on TEAEs and SAEs will be received by all members of the Study team.

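### The Related and Not Related definitions in section 8.3.3 overlap, and the causality scales do not fit the ADR definition, so one event can validly be coded as an ADR or as Not Related

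*Protocol*

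**What the plan says.** Section 8.3.3 first gives a two-way split of all AEs. An event is *Related* if it follows the drug in a reasonable temporal sequence, "or for which possible involvement of the drug cannot be ruled out, although factors other than the drug" may be responsible as well. An event is *Not Related* if it is "An AE that does not follow a reasonable temporal sequence from administration of a drug and/or that can reasonably be explained by other factors".

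The same section then gives a finer scale, to be applied to each ADR. Its six levels are Conditional / Unclassified, Unlikely, Possibly, Probably and Definitely related, and Not Applicable. *Unlikely related* means a timing that "makes a relationship improbable (but not impossible"), with another plausible explanation. *Possibly related* means reasonable timing with disease or other drugs as a competing explanation.

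Section 8.3.1.2 makes an event an ADR when "a causal relationship between a medicinal product and an adverse event is at least a reasonable possibility, i.e., the relationship cannot be ruled out".

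Section 8.3.4 has the CRF record causality for every AE on a list of seven: "not related, conditional, unlikely related, possibly related, probably related, definitely related, not applicable".

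The number of ADRs per arm is a safety endpoint (synopsis, Table 3.2, section 8.2). Section 8.3.1.3 defines a SUSAR as "any SAE where a causal relationship with the study product is at least reasonably possible" and that is not listed in the reference documents.

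**The concern.** Two classes meant to divide all AEs should exclude each other. Here *Related* is built with an *or* and tolerates other causes, while *Not Related* is built with an *and/or* and is satisfied by another cause alone. An event that fits the drug in time and could also be due to the injury, an intercurrent illness or another drug sits in both.

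The second problem is that the three causality instruments do not fit together. A scale reserved for ADRs should not need a level for improbable relationships or levels for cases that cannot be judged. The CRF list then applies nearly that scale to all AEs.

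What is at stake is the meaning of the ADR count, the tabulation of AEs by causal relationship in section 9.1.3, and the investigator's causality code as an input to the SUSAR decision.

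**Working it through.** No figure in the protocol bears on this, so the check is logical.

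**Inputs.** Three yes/no attributes taken from sections 8.3.3 and 8.3.1.2:
- T: the temporal sequence is reasonable.
- P: drug involvement cannot be ruled out. This is also the ADR test in 8.3.1.2.
- O: other factors reasonably explain the event.

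**Formulas.**
- Related = T or P.
- Not Related, as written = (not T) or O.
- Not Related, if *and/or* is merely changed to *and* = (not T) and O.
- Not Related, as the complement of Related = (not T) and (not P).

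| T | P | O | As written | *and* for *and/or* | Complement |
|---|---|---|---|---|---|
| no | no | no | Not Related only | neither | Not Related |
| no | no | yes | Not Related only | Not Related only | Not Related |
| no | yes | no | both | Related only | Related |
| no | yes | yes | both | both | Related |
| yes | no | no | Related only | Related only | Related |
| yes | no | yes | both | Related only | Related |
| yes | yes | no | Related only | Related only | Related |
| yes | yes | yes | both | Related only | Related |

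**Results.**
1. As written, 4 of 8 combinations meet both definitions, 2 meet only Related, 2 meet only Not Related and none meets neither.
2. Among the four combinations with P = yes, which meet the ADR test, three also meet Not Related. The only one that does not is reasonable timing without any other explanation.
3. The row (yes, yes, yes) is the protocol's own *Possibly related*. The row (no, yes, yes) is its *Unlikely related*.
4. Changing *and/or* to *and* leaves one combination in both classes, (no, yes, yes), and puts one in neither, (no, no, no). It is not a sufficient repair.
5. The complement wording leaves no overlap and no gap.

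These are counts of logical combinations, not expected proportions of events.

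**The three instruments side by side.** Section 8.3.1.2 treats a reasonable possibility and a relationship that cannot be ruled out as the same threshold. The finer scale separates them: *Unlikely related* is not excluded, but is hardly a reasonable possibility. That scale is restricted to ADRs in 8.3.3, whereas 8.3.4 applies its six levels plus *not related* to every AE and drops plain *Related*. No section says which of the seven levels make an AE an ADR.

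**The case against.** Several points on the other side have force.

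- **The recorded list gives the typical event a place.** Reasonable timing with an alternative cause is almost exactly *Possibly related*, and 8.3.4 already records one list for every AE. This stands, and it narrows the choice to *possibly* versus *not related*. It does not settle that choice, because the same facts also meet the written definition of *Not Related*.
- **Which categories count as ADRs in a table can be left to the SAP.** This is fair; the missing cut-off alone would not be a finding. But the investigator picks the code at data capture under definitions that allow opposite answers. A later cut-off cannot repair a code that was ambiguous when entered, and SUSAR decisions are made during the trial.
- **The impact is bounded.** Assessment is blinded (4.2.2), randomization is stratified by center (4.2.1) and safety is not formally tested (9.1.3). Differing habits between sites would not by themselves favour an arm. This stands.

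A reader might infer that a serious event could go unreported. The protocol does not support that. Section 8.3.4.1 sends every SAE, whatever its causality, to the CRO within 24 hours and requires the sponsor to be notified within 24 hours. The sponsor is responsible for SUSAR reporting (second section numbered 8.3.2), so only the causality input is at issue.

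A reader might also infer that an early headache with fitting timing could be *Unlikely related*. It could not, since that level requires a timing that makes the relationship improbable.

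**Conclusion.** The inconsistency is real and lies in the current text. The same event can validly be coded as an ADR or as *Not Related*. The consequence is limited to the descriptive ADR endpoint, the tabulation by causal relationship and the causality input to SUSAR classification. SAE reporting to the CRO and sponsor, TEAE and SAE counts, and the efficacy analysis are not affected. It should be corrected, but it does not threaten the trial's main result.

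The size cannot be derived from the document, because the share of AEs with a competing explanation is not given. It is tempting to use the pilot study in section 2.3.2, where one of the three AEs described among 36 treated patients was a headache, and to say that the ADR count could move by one in three. The protocol does not say whether that headache had another explanation, so the figure is not supported. Nor does it show that the overlap covers most events: unchanged pre-existing symptoms are not TEAEs under 8.3.1.1.

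The conclusion assumes that the definitions are applied as written and that no investigator instruction outside the protocol already resolves the overlap.

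**What to change.** Reconcile sections 8.3.1.2, 8.3.1.3, 8.3.3 and 8.3.4:

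1. Use the single list in 8.3.4 for every AE, and delete the wording in 8.3.3 that limits the finer scale to ADRs.
2. Word *Not Related* as the exact complement of *Related*: timing not reasonable and drug involvement ruled out. Changing *and/or* to *and* is not enough, as the table shows.
3. State which recorded categories count as an ADR and which count as reasonably possible for a SUSAR, consistent with the 8.3.1.2 test. Say explicitly where *unlikely*, *conditional* and *not applicable* fall. The rule should also cover an event that is *Related* on timing alone although involvement is ruled out, because that event does not meet the ADR test.

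The cost is a wording change and a revised CRF code list. The ADR count may come out somewhat higher. No additional data are needed.
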